- H2: Cortical activation measured by fNIRS from the visuomotor integration and the attentional network areas during the baseline phase will be lower in the children with DCD than in children with TD. Relative activation levels ( $[O_2Hb]$ ) in both networks during adaptation and consolidation will demonstrate opposite profiles in children with DCD (start low, end high) vs children with TD (start high and end low). In addition, acute intense exercise will narrow, but may not completely close, the gap between children with DCD who receive the exercise intervention and children with TD controls.
- H3: In a pilot study, combining fDCS technology that measures  $CMRO_2$  and rCBF with fNIRS technology will provide us with the possibility to obtain more accurate and robust information of the children's brain activity during learning than using fNIRS alone.

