$$y = a * e^{b*x} - c * e^{d*x}$$

where  $y$  is the error (epoch's mean),  $x$  is the epoch number and  $a$ ,  $b$ ,  $c$  and  $d$  are parameters. The initial rate of learning (RL) will be computed, as described in Coats (2014), as the first derivative of the first half of the function and evaluated at epoch 1 for both error variables IDE (RL-IDE) and RMSE (RL-RMSE). All individual exponential functions will be visually inspected for a plateau to assess that learning is achieved.

Progress towards increasingly skilled performance consists of the acquisition and stabilization of more effective movement patterns (Vereijken, Van Emmerik, Bongardt, Beek, & Newell, 1997). Inter-trial variability could be used to assess the stabilization level of the task. High values of variability are related to an early learning stage that explores new solutions for the task while low values of variability are associated with more skilled performers showing stable executions. Changes in variability across epochs in the acquisition set (i.e., rate of variability, RV) for both error variables (RV-IDE-SD and RV-RMSE-SD) will be also computed.

Normalized changes in concentration levels of hemodynamic variables during the different sets will be analyzed. Neural activation of each cortical area will be expressed as an increase of  $[O_2Hb]$  (also of  $CMRO_2$  and CBF in the pilot study) and a decrease in  $[HHb]$  (Mandrick et al., 2013). Qualitative analysis of the changes in these variables across trials will be performed to establish differences in hemodynamic patterns. Average and SD of the hemodynamic variables for each set will be calculated.

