A list of the principal tasks related to the research objectives are presented indicating members of the group involved. Critical tasks that could alter the expected timing (underlined) are related to the accessibility of the sample and DCD children detection.

- **Task 1.** Participant recruitment
  - Task1.1. Participant recruitment. Investigators involved: PI1, WT3, WT4. Duration: M1-36.
- **Task 2.** Objective 1
  - Task 2.1. Collection of participant's characterization data, including: Health status (PARQ), physical activity engagement (PAQ-C), academic and daily living activities performance (MABC-2 checklist), possible comorbidities report, regular medication intakes, possible psychosocial problems (Conners CBRS), exclusion criteria related-data, and the family-related information. Investigators involved: PI1, PI2, WT3. Duration: M2-40.

- Task 2.2. Intelligence quotient data collection using the Test of on-verbal intelligence version 4 (TONI-4). Investigators involved: PI1, PI2, WT3. Duration: M2-40.
- Task 2.3. Motor coordination data collection using the Movement assessment battery for children – second edition (MABC-2). Investigators involved: PI1, PI2, WT3. Duration: M2-40.
- Task 2.4. Participant's anthropometric data collection. Investigators involved: PI1, PI2, WT3. Duration: M2-40.
- Task 2.5. Estimation of participant's VO2max via the 20-meter shuttle run test (20mSRT). Investigators involved: PI1, PI2, WT3. Duration: M2-40.
- Task 2.6 Exercise intervention execution and motor learning (rotational visuomotor adaptation task) behavioral data collection. Investigators involved: PI1, PI2, RT1, WT3, WT4. Duration: M2-40.
- Task 2.7. Reduce data and carry bio-statistical procedures. Investigators involved: PI1, PI2, RT1, WT1, WT2, WT3. Duration: M7-45.
- Task 2.8. Produce results and disseminate according to dissemination plan. Investigators involved: PI1, PI2, RT1, WT1, WT2, WT3. Duration: M14-48.
- **Task 3.** Objective 2 and 3
  - Task 3.1. Brain activity data acquisition under resting state and baseline execution of the motor task (rotational visuomotor adaptation task without deviation of hand movements). Investigators involved: PI1, RT1, WT3, WT4. Duration: M2-40.
  - Task 3.2. Brain activity data collection during the acquisition and retention of the new motor skill (rotational visuomotor adaptation task with hand movements deviated 60 degrees clockwise). Investigators involved: PI1, PI2, RT1, WT3, WT4. Duration: M2-40.

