  - Task 3.3. Reduce data and carry bio-statistical procedures. Investigators involved: PI1, PI2, RT1, WT1, WT2, WT4. Duration: M7-45.
  - Task 3.4. Produce results and disseminate according to dissemination plan. Investigators involved: PI1, PI2, RT1, WT1, WT2, WT3, WT4. Duration: M14-48.
- **Task 4.** Return to society and preparation of future projects
  - Task 4.1. Development of DCD awareness booklets/brochures and website. Investigators involved: PI1, PI2, RT1, WT1, WT2, WT3. Duration: M1-4 (phase 1) and M42-48 (phase 2).
  - Task 4.2. Workshops to increase knowledge about DCD between parents and educators. Investigators involved: PI1, RT1, WT1, WT3. Duration: M1-4 (phase 1) and M42-48 (phase 2).
  - Task 4.3. Define methodological procedures and prepare documentation for future projects. Investigators involved: PI1, PI2, RT1, WT1, WT2, WT3, WT4. Duration: M43-48.

Given the large sample needed for this project and the total number of sessions that each participant will be engaged in, we estimate that data collection would last 39 months approximately (school vacations periods included). Therefore, we elaborated a work plan schedule of 4 years (Figure 4).

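### H2's start-to-end haemodynamic profile, if read within a set, rests on a qualitative reading with no stated rule or masking

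*Protocol*

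**What the plan says.** The Variables section, after defining the haemodynamic measures, states: "Qualitative analysis of the changes in these variables across trials will be performed to establish differences in hemodynamic patterns". The sentence that follows it provides an average and SD of each haemodynamic variable for each set. No criterion for a pattern, number of readers, agreement check or masking is given.

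H2, under Justification and Hypotheses, is directional. Of the relative [O2Hb] levels in the two networks while the task is learned and retained, it says that they "will demonstrate opposite profiles in children with DCD (start low, end high) vs children with TD (start high and end low").

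The Statistical analysis section plans these tests for the haemodynamic variables: ANOVAs on baseline means across the four groups; t-tests of CON-DCD against CON-TD in the adaptation set; Group x Time ANOVAs over the three retention tests; and Group x Exercise and Group x Exercise x Time ANOVAs for the effect of exercise.

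The work plan lists roles by task. Task 2.6 reads: "Exercise intervention execution and motor learning (rotational visuomotor adaptation task) behavioral data collection. Investigators involved: PI1, PI2, RT1, WT3, WT4". The brain-data analysis reads: "Task 3.3. Reduce data and carry bio-statistical procedures. Investigators involved: PI1, PI2, RT1, WT1, WT2, WT4". The Ethic treatment section says that identity is held in one secure file and coded elsewhere, to preserve anonymity.

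**The concern.** The protocol uses the verb *establish* for a qualitative reading. That makes the reading the means of reaching a conclusion about group differences, not an illustration of one. The expected answer is written into H2, and the analysis team knows it. Haemodynamic traces leave room for judgement, and without a rule fixed in advance a reader can find the predicted shape in an ambiguous curve. If the reader also knows which children have DCD and which exercised, nothing in the method corrects for that expectation, and no test stands behind the conclusion. At stake is the claim that DCD and TD children show opposite activation profiles while learning, and that exercise brings them closer.

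**Working it through.** No sample size, power or error rate is involved. The check sets three parts of the protocol side by side.

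**1. Which parts of H2 have a numerical test?**

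- Lower activation in DCD at baseline: ANOVA on baseline means across four groups.
- Exercise narrowing the gap: Group x Exercise ANOVA in adaptation, and Group x Exercise x Time in retention.
- Change across retention: Group x Time, where Time has three levels (1 h, 24 h, 7 days). Adaptation is not one of the levels.
- Start-to-end profile within a set: none.

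**2. Could the set mean and SD detect a within-set profile?** Take a profile that rises steadily through a set, with epoch values y1, y2, ..., yn. Reverse it, so that it falls: yn, ..., y2, y1. The sum of the values is the same, so the mean is the same. The squared deviations are the same set of numbers, so the SD is the same. Two groups with exactly opposite profiles would therefore give identical summaries to the planned t-tests and ANOVAs. Only an analysis that keeps the order of trials can tell them apart, and the only one in the protocol is the qualitative reading.

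**3. Who is listed for collection and for analysis?** From the work plan:

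| Role | Task 2.3 (MABC-2) | Task 2.6 (exercise, behavioural testing) | Task 3.2 (brain recording in learning) | Task 3.3 (brain-data analysis) | Task 3.4 (results) |
|---|---|---|---|---|---|
| PI1 | yes | yes | yes | yes | yes |
| PI2 | yes | yes | yes | yes | yes |
| RT1 | no | yes | yes | yes | yes |
| WT1 | no | no | no | yes | yes |
| WT2 | no | no | no | yes | yes |
| WT3 | yes | yes | yes | no | yes |
| WT4 | no | yes | yes | yes | yes |

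- Tasks 2.6 and 3.3 share PI1, PI2, RT1 and WT4: 4 of the 6 analysis roles, and 4 of the 5 exercise roles.
- Task 3.4 ("Task 3.4. Produce results and disseminate according to dissemination plan. Investigators involved: PI1, PI2, RT1, WT1, WT2, WT3, WT4") includes 5 of the 5 exercise roles.
- PI1 and PI2, both in Task 3.3, are also listed for the MABC-2, whose score is one of the criteria separating the cohorts.
- WT1 and WT2 appear in no recruitment or data-collection task (1.1, 2.1 to 2.6, 3.1, 3.2).

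**4. Does anything mask cohort or arm?** No masking of assessors, analysts or readers is stated. The identity coding removes names. It does not say that cohort or arm is removed from the files.

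**The case against.** The strongest reply is that a reader might infer more than the text contains.

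- **Readers who know the groups.** One might conclude that the reading is given to people who know each child's group. The protocol does not say so. The sentence is in the passive voice, Task 3.3 lists six roles without dividing the work, and knowledge of group is an inference from the task lists and the silence on masking. This objection stands. The point is exposure to bias, not a documented assignment of unmasked readers.
- **All of H2 untested.** H2 does not say that its profiles run within a set. It can be read as running from adaptation to the later retention tests. On that reading, the Group x Time ANOVAs test the retention leg. This also stands, and it limits the point to one component of H2.
- **A count of affected curves.** Multiplying children, sets and areas would assume that every individual curve is read separately. The protocol does not say whether individual or averaged curves are read, so no count is supported.
- **The visual check of the fitted learning curves.** This is a judgement by eye too, but it serves to confirm a plateau and is tied to no group comparison or exclusion. It does not belong to this point.
- **O2 is exploratory.** That is true of its wording, and it argues for calling the reading descriptive. It does not support a method said to establish differences.
- **A separate analysis plan might supply rules and masking.** It might; none was at hand. Masking of a subjective reading, however, has to be arranged before anyone views the files. The protocol already fixes the method and what the reading is meant to establish.

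**Conclusion.** The concern holds for one component of H2. If the predicted opposite profiles are meant within a set, the only analysis able to show them is a qualitative reading without a rule or masking, and the protocol says that it will establish differences. Four of the six roles listed for analysing the brain data are also listed for delivering the exercise intervention and collecting behavioural data, and the coding in place protects identity only. That component is open to expectation bias.

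The conclusion rests on two assumptions: that the within-set reading of H2 is at least one intended meaning, and that the people who carry out the reading come from those listed in Task 3.3. The size of any bias cannot be derived from the protocol. The baseline, exercise-gap and across-retention parts of H2 are not affected, because they have ANOVAs on set means. The point merits correction before the traces are read; it does not undermine the trial as a whole.

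**What to change.** In the Variables section:

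1. Replace *establish* with *describe*, and state that the qualitative reading is descriptive support only.
2. State that the reading is done on files recoded without cohort or arm, by team members who did not collect data. WT1 and WT2 are candidates from the task lists, provided they are unaware of group and able to read these signals; the protocol shows neither. Record and lock the classifications before codes are joined to groups.
3. Base any conclusion on the H2 profile on a computed measure: early-minus-late [O2Hb], or its slope over epochs. The Data reduction section already divides the adaptation set into epochs of 8 trials, which gives 312 / 8 = 39 epochs. Fix in advance which epochs count as early and late, or that the slope uses all of them.

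In the Statistical analysis section, test that measure between CON-DCD and CON-TD for O2.1, and by Group x Exercise for O2.2. Also state whether H2's profiles run within a set, across sets, or both. If a within-set profile is also claimed for the retention sets, extend the epoch definition to them (104 / 8 = 13 epochs each).

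The cost is a recoding script, the time to record and lock the classifications, and one extra derived variable. No new recording or visit is needed.

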## Statistical analysis

Age, gender, weight, handedness, physical activity engagement, and fitness level (estimated  $VO_{2max}$ ) measures were explored through one-way analysis of variance (ANOVA) to evaluate group differences. Non-parametric ANOVA will be used when necessary.

Descriptive statistics of all the scores /results obtained from the questionnaires answered by the parents and teachers, the anthropometric measures (height, weight, and BMI), and the tests conducted in sessions 1 (20mSRT) and 2 (TONI-2 and M-ABC2) will be used to characterize DCD and TD children (**O1.1**). Also, independent t-test will be applied to contrast the differences between the DCD and the TD cohorts (**O1.1**). Variables obtained from the rVMA will be used to elucidate and compare the motor learning ability of children with and without DCD while performing rVMA (**O1.2**) and the effect of acute exercise on this motor learning (**O1.3**), while data from the fNIRS will explore patterns of brain activation while learning a motor adaptation task in children with and without DCD and the effect of iE (**O2**). Data from fNIRS and dDCS collected during the pilot study will be used to assess the fDCS usability and point out the additional relevant information to use both optical technologies simultaneously (**O3**).

We will compare the mean baseline value for each rVMA and brain hemodynamics variables with ANOVAs to evaluate baseline performance across the four groups. Differences between the CON-DCD and CON-TD children groups (O1.2 and O2.1) on the motor learning (adaptation and retention phases) will be explored using independent t-tests in the adaptation set, while 2 (Group) x 3 (Time) ANOVAs with repeated measures will be used to analyze differences in the retention phases. Focusing on the effects of exercise (O1.3 and O2.2), possible differences in the adaptation set will be contrasted by 2 (Group) x 2 (Exercise) ANOVAs and retention tests will be analyzed by 2 (Group) x 2 (Exercise) x 3 (Time) ANOVAs with repeated measures. Association of the changes in brain activation variables with changes occurred in the rVMA variables will be explored using bivariate correlations and multivariate correlations (O2.3). Usability and additional information provided by fNIRS and fDCS will be evaluated qualitatively and contrasted brain activity levels obtained from both technologies using t-test and ANOVAs (adaptation: t-test (Technology); retention tests: 2 (Technology) x 3 (Time) ANOVAs) (O3).

Before any statistical test normality distribution will be tested for all variables via exploration of histograms, Q-Q plots and with the Shapiro-Wilk's normality test. When the normality assumption failed, variable transformation or non-parametric alternative tests will be adequately conducted. In all ANOVAs Greenhouse-Geisser sphericity-corrected values will be used when appropriate. Variables with initial group differences and significantly correlated with the dependent variable will be considered as potential covariates in the ANOVA analyses. Bonferroni *post hoc* analyses will be performed if significant differences are found. In addition, the effect size will be calculated using  $\eta^2p$  (0.01 small, 0.06 medium, 0.14 large effect). Statistical significance was set at  $p < 0.05$  for all analyses.

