## **ABSTRACT**

Developmental coordination disorder (DCD) is one of the most prevalent chronic conditions that affects about 35,000 children in Catalunya alone. Yet, it is not particularly known. DCD is a disorder characterized by a significant delay in motor skill performance and learning which carries functional consequences in daily activities and academic performance. Without proper and timely diagnosis and intervention, these consequences may persist until adulthood. Physical activity, as a potential intervention, has been proven to improve motor learning (adaptation and consolidation) in children, even in those with some disorders. However, no studies have examined the effect of a short bout of physical exercise on motor adaptation and consolidation in children with DCD. Furthermore, the potential role of perceptual-motor integration and attention as mediators of learning has been examined via neuroimaging in pediatric populations, but not in children with DCD. Therefore, the primary aims of this project will be (a) to examine the effect of acute exercise on motor learning (adaptation and consolidation) while performing a rotational visuo-motor adaptation task (rVMA) in children with and without DCD, (b) to explore cortical activation in the visuomotor integration and the attentional network areas while learning the rVMA task in children with and without DCD under rest or post-exercise conditions, and (c) to explore via a pilot study the combined use of two optical neuroimaging techniques (functional near-infrared spectroscopy, fNIRS, and functional diffuse correlation spectroscopy, fDCS) to measure cortical activation in the visuomotor integration and the attentional network areas while learning a motor adaptation task in children with and without DCD under rest or post-exercise conditions. We will recruit 120 children from 6-8 schools (60 DCD, 60 controls) and randomly assign them to either exercise or rest prior to performing a rotational visuo-motor adaptation task. The exercise will be a 13min shuttle run task. Adaptation and consolidation of the learned task will be evaluated via two error variables and 3 retention tests (1h, 24h and 7 days post adaptation). Cortical activation will be registered via fNIRS during the baseline, adaptation and consolidation phases to estimate sustained attention. As a pilot study, the brain activity of a subset of 10 children of each group will be recorded using a hybrid optical neuroimaging device (fNIRS + fDCS). We expect to find exercise benefits on both, motor learning and attention, in children with DCD so that their profiles are closer to those of children with typical development. The results of this project will provide further evidence to: (a) better characterize children with DCD; (b) establish acute exercise as a potential intervention to improve motor learning and attention, explored for the first time through concurrent brain imaging and behavioral assessments in DCD children; (c) design educational materials for educators and families related to children with DCD; and (d) verify that combining optical technology provide us with the possibility to obtain more accurate and robust information of the children's brain activity during learning.

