In order to examine the combined effect of acute exercise and learning on children's brain activity, widely used neuroimaging techniques are either too expensive, or do not allow for in-situ assessment (i.e., same location where learning is occurring, in our case, children's school). Optical technologies have been utilized and suggested as potential and promising tools to fully study the alterations of the brain networks. Perhaps most importantly, the features of the new technological approach (non-invasive, quantitative, safe, inexpensive and portable) and the characterization of brain activity using fNIRS will allow us to conduct studies in-situ (i.e., children's school) with robust results, including estimation of what brain areas are more or less activated while learning in children with DCD. In addition, combination of two optical techniques, fNIRS and DCS, has the potential to add new reliable information of the children's brain activity during learning which open the door to conduct a pilot study to verify this potential. This knowledge is hypothesized to assist in the design of better, more targeted interventions. In addition, exercise benefits in learning, if confirmed in this population, could also be integrated as part of effective educational interventions for children with DCD. Our research hypotheses are arranged around these concepts.

- H1: Children with DCD will show worse motor learning (slower movements, more variability, slower rate of learning, and worse consolidation) than

typically develop (TD) children when facing a rotational visuomotor adaptation task (rVMA). Performing an acute intense exercise bout before rVMA will improve consolidation in TD and DCD children. In addition, exercise will narrow the gap between children with DCD and children with TD. Based on the null exercise effect on adaptation previously found in TD children, we have no predictions for DCD children.

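### The exercise benefit in children with DCD has no named, unconditional EX-DCD versus CON-DCD comparison; only an unspecified, conditional post hoc could test it

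*Protocol*

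**What the plan says.** The Abstract announces: "We expect to find exercise benefits on both, motor learning and attention, in children with DCD". H1 (Justification and hypotheses) makes two separate claims about exercise. The first is about each cohort: "Performing an acute intense exercise bout before rVMA will improve consolidation in TD and DCD children". The second is about the difference between cohorts: "exercise will narrow the gap between children with DCD and children with TD". H1 makes no prediction for the adaptation phase in DCD.

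For the exercise objectives (O1.3 and O2.2), Statistical analysis names two models. For adaptation, "possible differences in the adaptation set will be contrasted by 2 (Group) x 2 (Exercise) ANOVAs". For retention, "retention tests will be analyzed by 2 (Group) x 2 (Exercise) x 3 (Time) ANOVAs with repeated measures". The follow-up is a Bonferroni post hoc clause: such "analyses will be performed if significant differences are found". The clause does not say which comparisons are made, how many form the family, or which ANOVA term triggers them.

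The same section does name a direct two-group comparison for a different objective: "Differences between the CON-DCD and CON-TD children groups (O1.2 and O2.1"). It names no counterpart for EX-DCD against CON-DCD.

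**The concern.** The Introduction cites evidence that exercise aids consolidation in TD children and says that the project was set up to learn whether children with DCD could benefit. The DCD effect is therefore the main question, and the TD effect is largely background. The planned tests are not aimed at that effect. The main effect can be carried by the cohort in which a benefit is already expected. The interaction has a true null when exercise helps both cohorts equally, which is an outcome that the first H1 claim allows.

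Two things are at stake. A pooled effect driven by TD children may be presented as support for exercise in DCD, and the Protocol plans to take its results to schools. Conversely, a real DCD effect may be missed or left untested, because its only test is conditional and Bonferroni-adjusted over an unnamed family.

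**Working it through.** **Inputs.** From the sample-size paragraph (Participants): 30 children in each of four cells, alpha 0.05, exercise effect size 0.55, cohort effect size 0.78. Assumed, because not stated: two-sided tests, effect sizes as Cohen's d, equal SDs (set to 1), no attrition. The base case treats the retention score as one value per child.

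**The plan's own figure.** The Protocol gives no power for the DCD contrast. It gives 12-26 per group for TD versus DCD. With n = 2(1.960 + 0.842)²/d², d = 0.78 gives 15.70/0.608 = 25.8, so 26, which matches the upper end. d = 0.55 gives 15.70/0.3025 = 51.9, so 52 (53 by the t distribution). The lower end, 12, is not reproduced on this metric. That is a separate matter and does not decide this point.

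**Step 1: the nulls.** Let T and D be the true exercise effects in TD and DCD children.
- Exercise main effect: null (T + D)/2 = 0, SE = √(1/n).
- Group x Exercise: null T − D = 0, SE = √(4/n).
- EX-DCD versus CON-DCD: null D = 0, SE = √(2/n).

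Terms involving Time ask whether these effects change across the three retention tests. Only the third line is the DCD question.

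**Step 2: only TD children benefit (T = 0.55, D = 0, n = 30).**
- Main effect noncentrality: 0.275/√(1/30) = 1.506. Interaction: 0.55/√(4/30) = 1.506. Each has power 0.32 on 116 df.
- Significant main effect with non-significant interaction: about 0.32 × 0.68 = 0.22 (simulation 0.22).
- Direct DCD contrast, false claim of benefit: 0.025.

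Sensitivity of the 22%: TD-only effect 0.78 gives 25%; 1.10 gives 13%; 25 per cell at 0.55 gives 20%. If averaging three retention tests reduces the SD (between-test correlation 0.7 to 0.3, assumed), it is 23-25% at 0.55.

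**Step 3: both cohorts benefit (T = D = 0.55).**
- Main effect: significant in 85%.
- Interaction: significant in 5%, as it should be, since its null is true.
- Direct DCD contrast: noncentrality 0.55/√(2/30) = 2.13; power 56% with the model error term (116 df), 55% as a 30 versus 30 t-test.
- Post hoc DCD pair after any significant exercise term: about 44% with 2 Bonferroni pairs, about 29% with 6.
- Post hoc DCD pair only after a significant interaction: about 2%.

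**Step 4: what the direct contrast would need.** For 80% power at 0.55 it needs 53 DCD children per arm (t); the trial has 30. With correlations of 0.7, 0.5 and 0.3 between the retention tests, its power at a per-test effect of 0.55 is about 65%, 73% and 82%.

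**The case against.** The strongest reply is that the plan does contain a test of the DCD effect. The post hoc clause applies to a design with four named cells, and EX-DCD versus CON-DCD is one of the pairs. A reader might infer that the DCD effect is never tested at all. The documents do not support that, because the clause could cover this pair. What remains is that it is conditional and unspecified. A significant two-level Exercise factor without an interaction needs no post hoc, so in the very case that matters the DCD pair need not be run.

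A reader might also take the 22% (or the 32% for the pooled effect alone) as the plan's false-claim rate for DCD. It is not. The Protocol states no rule for turning ANOVA terms into a DCD claim. If the post hoc DCD pair is run after any significant exercise term, a false DCD benefit appears in only about 0.4-1.3% of trials (6 to 2 pairs), below the 2.5% of the direct contrast.

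Third, the interaction is the right test for H1's gap-narrowing sentence. It is tempting to say that it costs H2 the difference between 56% and 5%. That would require reading "the gap between children with DCD who receive the exercise intervention and children with TD controls" as a comparison with CON-TD specifically, although the Abstract uses 'controls' for the whole TD cohort. It would also carry an effect size from a behavioural error measure over to cortical activation, for which the Protocol gives none.

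Finally, follow-up contrasts are often left to an SAP, and a factorial ANOVA is a standard analysis of a 2 x 2 design. That lowers the severity. It does not remove the point, because the Protocol itself fixes the tests for these objectives and they do not match its own DCD hypothesis.

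**Conclusion.** The point holds as a should-fix. The nulls in Step 1 follow from the model and need no simulation: no named test isolates the exercise effect in DCD children, and the one clause that could do so is conditional and names no comparisons.

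The consequence is an ambiguous result pattern in about 22% of trials under a TD-only effect of 0.55. Under an equal effect of 0.55 in both cohorts, the chance of detecting the DCD effect falls from about 56% to about 29-44%, or to about 2%, depending on how the post hoc clause is read. These figures rest on the assumptions listed in the working. The point concerns retention; it matters less for adaptation, where H1 predicts nothing for DCD.

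It does not follow that both cohorts' contrasts must be significant before H1 can be supported. That rule would have about 0.56 × 0.56 = 31% power at 0.55, and it is a debatable trade-off that this point does not need.

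**What to change.** Keep the same models and add to Statistical analysis:
- EX-DCD versus CON-DCD on retention (averaged over the three tests, or at one named test) is the planned test of exercise benefit in DCD. It uses the model error term, is reported with a 95% CI, and is run whatever the main effect and interaction show.
- The matching EX-TD versus CON-TD contrast is reported with its 95% CI.
- Group x Exercise remains the test of H1's gap-narrowing claim.
- A significant pooled Exercise effect is not by itself evidence of benefit in DCD.

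This costs wording only: same data, same model. The drawback is that the DCD claim then rests on 60 children, with about 55% power at d = 0.55. The sample-size paragraph should state that figure, alongside the roughly 53 per arm that 80% power would need.
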